## Abstract

**Background:**

Cigarette smoking is much more prevalent among young people experiencing homelessness than in the general population of adolescents and young adults. Although many young homeless smokers are motivated to quit, there are no empirically-evaluated smoking cessation programs for this population. It is important that any such program address the factors known to be associated with quitting-related outcomes among homeless young people, to provide ongoing support in a way that accommodates the mobility of this population, and does not rely on scarce service provider resources for its delivery. The objective of this project is to develop and pilot test a text messaging-based intervention (TMI), as an adjunct to brief cessation counseling and provision of nicotine patches, to help homeless young people who want to quit smoking.

**Methods/design:**

This pilot study will utilize a cluster cross-over randomized controlled design with up to 80 current smokers who desire to quit and are recruited from three drop-in centers serving young people experiencing homelessness in the Los Angeles area. All participants will be provided with a minimum standard of care: a 30-min group-based smoking cessation counseling session and free nicotine replacement. Half of these smokers will then also receive the TMI, as an adjunct to this standard care, which will provide 6 weeks of ongoing support for quitting. This support includes continued and more intensive education regarding nicotine dependence, quitting smoking, and relapse; does not require additional agency resources; can be available “on demand” to users; and includes features to personalize the quitting experience. This study will investigate whether receiving the TMI adjunct to standard smoking cessation care results in greater reductions in cigarette smoking compared to standard care alone over a 3-month period.

**Discussion:**

This study has the potential to address an important gap in the clinical research literature on cigarette smoking cessation and provide empirical support for using a TMI to provide ongoing assistance and support for quitting among young smokers experiencing homelessness.

*Trial registration* ClinicalTrials.gov Identifier NCT03874585. Registered March 14, 2019, https://clinicaltrials.gov/ct2/show/record/NCT03874585.

## Background

The goal of this project is to conduct a pilot evaluation of a text messaging-based smoking cessation program for young people experiencing homelessness. We are specifically interested in the “unaccompanied homeless youth” population, which is typically defined as individuals up to age 25 that are not currently living with or getting significant financial support from a parent or guardian, and who also have spent the previous night in a homeless setting (e.g., friend’s couch, street, homeless shelter) because of no place else to go [1–3]. The annual point-in-time U.S. homeless counts show an increasing number of unaccompanied young people experiencing homelessness, with the most recent count finding that 36,361 such young people are homeless on any given night [4]. In addition to living in poverty and being exposed to dangerous conditions inherent to street living, young people experiencing homelessness report high rates of cigarette smoking that put them at increased risk for the significant negative health effects associated with tobacco use [5].

## Cigarette smoking is prevalent among young people experiencing homelessness

Studies of unaccompanied homeless youth, which have tended to include both adolescents and emerging adults, have found that approximately 70% are current (past 30 day) cigarette smokers [6–8]. Further, 71% to 95% of these young smokers experiencing homelessness report smoking daily and 47% to 65% report smoking a half of a pack or more per day [8, 9]. These rates are substantially higher than in the general population of adolescents and young adults [10]. Further, research on homeless adolescents and young adults has found that most report one or more particularly high-risk smoking behaviors such as smoking shared cigarettes (96%), smoking discarded butts (71%) and filters (46%), and blocking filter vents (39%) [11]. Nearly half of young homeless cigarette smokers report rolling their own cigarettes, which may be filled with used tobacco obtained from discarded butts [12]. These practices may heighten their exposure to toxins and susceptibility to highly infectious diseases such as influenza, infectious hepatitis A, and tuberculosis [13, 14]. The health of homeless young people is adversely affected by unsafe living environments, nutritional deficiencies, mental health problems, problematic substance use, and insufficient access to health services [8, 15–18]. Adding tobacco use to the mix promises to further impair their already compromised health functioning [19].

## Young people experiencing homelessness are interested in formal smoking cessation services

The vulnerable population of young people experiencing homelessness has been largely overlooked in efforts to reduce smoking. Very few studies have examined the correlates of smoking among homeless adolescents and young adults [8, 20, 21], and there are currently no empirically-evaluated smoking cessation programs that specifically address the needs of this population. Yet, young smokers experiencing homelessness are motivated to quit smoking. For example, in a sample of nearly 300 homeless adolescents and young adults recruited from street venues, we found that almost half (43%) were motivated to quit in the next 30 days, and 76% of those who were motivated to quit were interested in using a nicotine replacement product and/or smoking cessation counseling to help them quit [9, 22]. Our work has found that homeless young people who are interested in quitting enjoy the camaraderie and peer support that group-based programs offer [23]. Thus, an initial group-based smoking cessation counseling session could provide a key opportunity to strengthen their motivation to quit and provide nicotine replacement medication. Yet, ongoing support is likely needed to help keep these young people engaged and commited to quitting smoking.

## Service providers consider smoking cessation a priority, yet have limited resources

Service providers are interested in helping homeless young people quit smoking, but few programs are currently offered [24, 25]. Our interviews with service providers found that nearly all (95%) were interested in offering cessation programming, but only one had an ongoing policy for helping their smoking clients (referrals to the California Smokers’ Helpline). The most commonly cited barrier to implementing a formal cessation program on site was lack of resources and staff training; thus, providers indicated a strong preference for cessation programs that required fewer resources (e.g., single session rather than multi-session treatment) but were also intensive enough to keep the client engaged and supported. A mobile health (mHealth)-based tool that provides ongoing support for quitting is likely a more sustainable approach than one that would rely on additional service provider resources.

## Text messaging interventions (TMIs) may be a promising approach

A recent Cochrane meta-analysis of randomized controlled studies that had follow-ups of 6 months or longer found that TMIs increased quit rates by 50–60%, both when the TMI was compared to minimal support and when it was tested as an adjunct to other forms of cessation support [26]. While these studies were mostly based on general adult samples, with only four studies specifically targeting young adults, using a TMI for smoking cessation may be a promising approach for young smokers experiencing homelessness. Nearly universal cell phone ownership among young people experiencing homelessness [27] holds great potential for offering ongoing support for behavior change as an adjunct to face-to-face services. A recent study using text messaging for daily data collection among homeless young people found it to be both acceptable and feasible; for example, individuals reported that receiving the texts made them feel that someone cared about them and encouraged them to self-reflect on their life [28]. There is growing appreciation that cell phones are not a luxury for those experiencing homelessness, but rather a necessity in terms of helping them maintain social and service contacts [29, 30]. Indeed, a number of recent initiatives have focused on increasing homeless individuals’ access to mobile technology for these purposes [31].

A tailored approach to smoking cessation which combines a single group counseling session and nicotine replacement with a TMI that is tailored to the circumstances of young smokers experiencing homelessness and the key factors that are known to be particularly relevant to their smoking cessation [9] could help circumvent the formidable barriers to quitting in this population. Such a TMI adjunct to a group-based treatment can provide ongoing information and support for quitting. This is especially important in service environments where both resources and the window for intervening with these young people are limited. Of course, there is much to learn about the feasibility of using TMIs for young people experiencing homelessness. For example, their cell phones may be more prone to loss or theft, or limitations in terms of data plans and functionality (ability to access websites, staying charged). These types of issues will be examined in this pilot study.

## The present study

The considerable evidence for the efficacy of TMIs to support quitting behavior suggests that this approach should be a public health priority. Further, innovative strategies are needed that can capitalize on existing motivation and initiative to quit smoking among young people experiencing homelessness, and provide the necessary resources and ongoing support to help them achieve their cessation goals. This study protocol describes our work to develop and pilot test a TMI designed to help young people experiencing homelessness to quit smoking.

## Methods/design

### Overview

This pilot study involves a cluster cross-over randomized controlled design [32–34] with up to 80 current smokers who desire to quit and who are recruited from three drop-in centers serving young people experiencing homelessness in the Los Angeles area. Two of the drop-in centers are approximately a two mile drive from each other, with the third drop-in center being approximately a 10–15 mile drive from the others. The unit of analysis will be the individual, but individuals will be assigned to groups (standard care alone vs. TMI adjunct) based on the drop-in center where they are seeking services. All participants will receive standard care: a 30-min group-based smoking cessation counseling session and free nicotine replacement. Half of these smokers will then also receive the TMI, as an adjunct to this standard care, which will provide 6 weeks of ongoing text messaging support for quitting. This ongoing support includes continued and more intensive education regarding nicotine dependence, quitting smoking, and relapse; does not require additional agency resources; can be available “on demand” to the user; and includes features to personalize the quitting experience. During the field period, each drop-in center will alternate in delivering these two treatments, offering one group-based smoking cessation counseling session every other month (to reduce possible contamination between conditions), with the type of treatment delivered first at each drop-in center being randomly determined. This pilot study will investigate whether receiving the TMI adjunct to standard smoking cessation care results in greater reductions in cigarette smoking compared to standard care alone over a 3-month period.

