Enrolled participants will complete their baseline survey while waiting for the 30-min group-based smoking cessation counseling session to start. After the counseling session, participants randomized to the TMI condition will begin receiving 6 weeks of text messages to their personal cell phone. Three months after the baseline survey, all participants will receive a follow-up survey. We expect a very high retention rate at 3-month follow-up based on the 91% retention rate we achieved at 3-month follow-up in a recent evaluation of a substance use and sexual risk reduction program involving 200 homeless young people conducted at some of the same study sites participating in this project [38]. We will use a number of innovative retention procedures that have helped us limit attrition with this transient population, such as collecting tracking information on their hangouts, places used for sleeping outdoors, and social networking sites; see our previous work for a detailed description of these procedures [39]. Figure 1 shows participant flow through the study, and Fig. 2 contains a SPIRIT (Standard Protocol Items: Recommendations for Interventional Trials) flow diagram of the RCT schedule of enrollment, interventions, and assessments.

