### Group counseling session and nicotine replacement

Participants in both conditions (standard care alone and TMI adjunct) will receive a 30-min counseling session, up to an 8-week supply of nicotine patches, and handouts on quitting smoking and dealing with cravings. The counseling session will be delivered in a small group setting at each of the drop-in centers. As mentioned earlier, each drop-in center will offer one group smoking cessation counseling session every other month, alternating in delivering the “standard care alone” vs. “TMI adjunct” treatment (with the type of treatment delivered during the 1st session at each drop-in center randomly determined). The counseling session will follow the 5 A’s format (Ask; Advise; Assess; Assist; Arrange) recommended in the 2008 U.S. Department of Health and Human Services Clinical Practice Guidelines for treating tobacco use and dependence [42, 43]. The session will be similar to our previous clinical research with adult smokers [44, 45]. However, it will be informed by our formative work and incorporate the content particularly relevant to young people experiencing homelessness (e.g., economic costs associated with smoking; health risks associated with free tobacco obtained through high-risk smoking practices) and use language appropriate for the young adult population. Participants will be asked to set a quit date and given an initial 4-week supply of nicotine patches with instructions on its use that follow package insert guidelines and potential side effects (participants will be able to get an additional 4-week supply of nicotine replacement, if they are interested; thus, they will have access to up to 8 weeks of nicotine replacement, a standard recommended length of treatment. Dosing instructions are tailored based on daily smoking rate. Two trained facilitators will be present at each session, one to deliver the intervention and the other to assist with the baseline survey, distributing materials, answering questions, and helping set up the TMI for those assigned to receive it.

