### TMI adjunct to standard of care condition

At the end of the group counseling session, participants randomized to the TMI condition will be signed up to receive the text messaging-based intervention. As shown in Fig. 3, the intervention has a strong theoretical basis in Social Learning Theory (i.e. smoking is related to both modeling of others’ behavior and perceptions about the behavior of others [46, 47]); Decision Making Theory (i.e. decisions about engaging in smoking are often emotional and therefore problem-focused coping skills are needed [48, 49]); and (c) Self-Efficacy Theory (i.e. building confidence about quitting will increase the likelihood of a successful quit attempt [50]). Participants assigned to the TMI will receive automated text messages for 6 weeks, which is within the range of other TMIs for smoking cessation [51]. Text message frequency and content is tailored to whether it is a pre-quit day, quit day, early post-quit day (within 14 days of quitting), or late post-quit day (15 + days after quitting) [52], with frequency being highest early in the quitting process (i.e., on the quit and early-quit days) and then tapering down. See Table 2 for the TMI text flow and samples of text messages.

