#### Preliminary analyses

Although participants will be randomly assigned (in groups of about 5–7 individuals) to either the TMI Adjunct or Standard Care Alone conditions, imbalance between the two groups on some of the baseline characteristics may occur. However, since assignment to treatment condition is random, any differences that arise are due to random chance [57, 58]. We will present balance tables of baseline data to confirm the two groups are similar. In all relevant analyses, we will control for variables that are expected to predict the outcome by including them as covariates in the models.

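### Only the first session at each of three centres is randomised and the rest alternate, so most conditions are foreseeable at recruitment and baseline differences cannot all be put down to chance

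*Protocol article*

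**What the plan says.** The Overview of the protocol article describes a cluster cross-over design at three drop-in centres. It says that "each drop-in center will alternate in delivering these two treatments", "with the type of treatment delivered first at each drop-in center being randomly determined". The section on the group counselling session repeats the rule: "with the type of treatment delivered during the 1st session at each drop-in center randomly determined". The Limitations section confirms that each centre serves both conditions in alternation. An individual's condition follows from where the person attends: "individuals will be assigned to groups (standard care alone vs. TMI adjunct) based on the drop-in center where they are seeking services".

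Recruitment is open, by flyers and announcements at the centres, followed by screening and consent by research staff. The order of events on the day is then: "Enrolled participants will complete their baseline survey while waiting for the 30-min group-based smoking cessation counseling session to start". The texting arm is set up last: "At the end of the group counseling session, participants randomized to the TMI condition will be signed up". A facilitator present at the session helps with that set-up.

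Preliminary analyses describes participants as randomly assigned in groups of about 5–7 and states that "since assignment to treatment condition is random, any differences that arise are due to random chance". The Limitations section is more cautious. It says a check of baseline balance is needed because randomisation is not at the individual level. It offers covariates, possibly propensity weights, and site as a fixed effect.

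**The concern.** Strict alternation carries no randomness after its first step. Anyone who knows which condition the last session at a centre delivered knows which comes next. Facilitators learn each session's condition because they help set up the texting programme. Announcing, screening and consenting for the next session all come after that knowledge is available. If it influences who is approached, encouraged or scheduled, the two arms can differ in ways that randomisation did not produce.

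The factor most likely to differ is motivation to quit, which also drives abstinence and is hard to measure fully. The article's main analytic goal is a preliminary effect size for a larger trial, and selective enrolment would distort that quantity directly. The statement about chance would also lead a reader to dismiss any imbalance that did appear.

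**Working it through.** **Inputs.** From the Overview: three centres, first condition random at each, alternation afterwards. From Power Considerations: up to 80 participants, about 5–7 per group, 90% follow-up, ICC 0.05. The number of sessions is not stated and is derived here.

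**The plan's own figure.** Follow-up per condition = 0.90 × 80 / 2 = 36. Effective sample size = 36 / (1 + 5 × 0.05) = 36 / 1.25 = 28.8, as stated. The factor 5 is 6 − 1, so the plan works with an average group of 6. The present point does not depend on the power calculation; the figure serves only to confirm the group size.

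**Number of sessions.**
- Groups of 7: 80 / 7 = 11.4, so about 12 sessions.
- Groups of 6: 80 / 6 = 13.3, so about 13.
- Groups of 5: 80 / 5 = 16.

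**Sessions fixed by alternation**, (S − 3) / S, where S is the number of sessions and 3 of them are first sessions:
- S = 12: 9 / 12 = 75%.
- S = 13: 10 / 13 = 77%.
- S = 16: 13 / 16 = 81%.

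**With order drawn for successive pairs within a centre.** The first session of each pair is unpredictable and the second is deducible.
- S = 12, four per centre: 6 of 12 = 50%.
- S = 13, split 5, 4 and 4: 2 + 2 + 2 = 6 of 13 = 46%, because the odd session opens an unfinished pair.

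**The passages side by side.** The Overview and the counselling section make three starting conditions random. Preliminary analyses treats every group of 5–7 as randomly assigned. Both cannot be right: of 12–16 groups, only the first at each centre has its condition drawn directly, and the others follow from it. Moreover, even a randomly drawn sequence supports the statement about chance only if recruitment cannot respond to it. Here most participants are recruited after their session's condition can be worked out.

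**Secondary arithmetic.** Three starts give at most 2³ = 8 schedules. If the starts are independent, all three centres start alike with probability 2 / 8 = 25%. If they also share a calendar, condition would then line up with odd versus even session slots.

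**The case against.** The strongest reply is that the scheme has a stated rationale and the study is a pilot. Individual randomisation was rejected because of contamination and because clients might feel refused a service. Alternation makes each centre its own control and largely balances slow trends over time. Recruitment procedures are the same at every centre. The Limitations section already acknowledges that randomisation is not individual and plans adjustment. All of this stands, and it lowers the weight of the point.

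It does not remove the point. Covariates and propensity weights correct only measured differences, site effects handle only differences between centres, and the article itself concedes that adjusting for several covariates may not be feasible at this sample size.

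It is also fair to say that the article does not report staff being told the sequence, and that a full protocol might describe concealment. However, late disclosure alone cannot hide a strictly alternating order once a centre's first condition has been seen.

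Three stronger readings are tempting, and the documents do not support them:
- *The trial cannot reach significance, because the smallest two-sided randomisation p-value is 2 / 8 = 0.25.* No randomisation test is planned. The article specifies logistic regression and a difference-in-differences model, for preliminary estimates.
- *Condition is completely confounded with calendar time.* This needs independent starts and a shared calendar, neither of which is stated. Even then the alignment is with odd versus even slots, and both conditions recur through the field period.
- *Clients will wait for the texting round.* Nothing in the article shows that clients know the sequence, and sessions run only every other month in a mobile population.

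**Conclusion.** The point holds as a matter of structure: about 9–13 of the 12–16 implied sessions (75–81%) have a condition that staff can foresee before they recruit for them. The first session at each centre is the exception. The conclusion assumes that groups run at about 5–7, that total enrolment is near 80, and that those who recruit know, or can learn, the condition of the preceding session.

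Selective recruitment is a risk inferred from this scheme, not something the documents report, and no figure in them allows its bias to be sized. The count of 8 schedules and the 25% chance of like starts describe how little is randomised; they do not measure that bias.

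The statement under Preliminary analyses is too strong for the scheme and needs to be reconciled with the Overview, the counselling section and the Limitations section. For an estimation-focused pilot the matter should be corrected, but it does not undermine the study as a whole.

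**What to change.** 1. Generate centrally, for each successive pair of sessions within a centre, a random order (texting then standard, or standard then texting). Every centre still serves both conditions equally over each completed pair, and the spacing of sessions is unchanged.
2. Disclose the condition to on-site staff and participants only at the end of the session, after consent, baseline survey and counselling. This fits the existing flow, since both arms receive the same session and sign-up for texts already comes last.
3. Reword Preliminary analyses to say that only the starting order (or the pair order, if changed) is random, that recruitment follows it, and that imbalance related to recruitment is possible. Refer there to the baseline checks in the Limitations section.

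The cost is a short central list and one sealed or emailed assignment per session. There are two drawbacks. Consecutive sessions at a centre may share a condition. The second session of each pair also stays deducible, so foreknowledge falls from about three quarters of sessions to about half and is not eliminated.
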